#### Clinician acceptability

Clinical acceptability will include all those involved in the treatment pathway and will be assessed within 5 working days of treatment delivery *for Arm 2 patients only*. Clinicians may be asked to complete the questionnaire up to 3 times to inform analysis as to whether perceptions change over time, for example, with increasing familiarity/exposure to the novel workflow.

Involved clinicians will be identified by the Collaborating Investigator or a member of the Lawson Health Research Institute Clinical Research Unit based on the electronic care path/treatment record.

On a clinician’s first encounter, an electronic version of the Clinician LOI/Consent will be emailed to their institutional email address. All staff will be aware of the possibility of receiving the LOI/Consent as they will be informed prior to opening the study at a staff meeting/inservice and by an email from the Principal and Collaborating Investigator. If/when the e-consent is completed and received, an e-version of the questionnaire will then be sent to the clinician.

Clinicians will be required to indicate how many times they have previously participated in the dCT-enabled treatment planning workflow on the questionnaire, but will only be required to complete one e-consent form. They will be advised of their right to withdraw participation at any time and for any reason, and that completing one questionnaire does not obligate them to complete further questionnaires.

### Scalability

Scalability will be determined by the outcome of program leadership’s evaluation of the completed ISAT [23]. The ISAT will be completed by stakeholders involved in the provision of the Arm 2 workflow and will include representation from RO, Medical Physics, Radiation Therapy (CT and Treatment Delivery) and Trial Investigators. The assessment will be submitted to program leadership and rated for scalability. Possible recommendations include: (i) Merits scale up, (ii) Promising, but further information/planning is warranted, and (iii) Does not merit scale up.

For the purpose of this trial, “scaling up” would include dosimetric calibrations of regional affiliate’s diagnostic imaging machines to enable expanded patient eligibility.

## Statistical considerations

### Randomization

Patients will be randomized in a 1:2 ratio between the current standard treatment workflow (Arm 1) and the experimental treatment workflow (Arm 2). This will be performed using permuted block design with block size known only to statistician until analysis is completed. The randomization sequence is known only to the statistician and uploaded into a restricted-access database (REDCap) housed on secure hospital servers at LHSC. Upon enrollment of a patient, the database will be accessed by the trial co-ordinator or collaborating investigator to obtain the next intervention in the random sequence, which will then be assigned to the patient.

### Sample size calculation

Based on a review of recent same-day treatments at the London Regional Cancer Program (LRCP), the estimated TIC in the standard arm of this trial will be 4.8 hours, with a standard deviation of 2. We hypothesize that in the experimental arm, the estimated TIC will be 2.5 hours, with the same standard deviation. Using a two-sided, two-sample t-test, with a 1:2 randomization, alpha of 0.05 and power of 80%, adjusting for 10% dropout, 33 patients are required, 11 in the standard arm and 22 in the experimental arm.

### Statistical analysis plan

Patients will be analyzed in the groups to which they are assigned (intention-to-treat). Comparisons between treatment arms for TIC (primary endpoint) will be performed using the two-sample t-test. TIC data is anticipated to be normally distributed. In the event such data is not normally distributed, non-parametric testing using the Wilcoxon rank sum test will be substituted as appropriate. For the secondary endpoints for efficacy (rate of plan deliverability and rate of plan acceptability on blinded review of dose distributions) and acceptability (stakeholder evaluations based on Likert scale), differences between treatment arms will be compared using the Chi-square test or Fisher’s exact test as appropriate. For the secondary endpoint for scalability based on the ISAT, differences between treatment arms will be compared using the two-sample t-test or substituted with Wilcoxon rank sum test if such data is not normally distributed, similar to primary endpoint.

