## Study design

This will be a pragmatic, randomized, controlled, open-label, feasibility trial.

All study activities will take place at the London Regional Cancer Program in London, Ontario, Canada.

Patients will be randomized in a 1:2 ratio between the current standard treatment workflow (Arm 1) and the experimental treatment workflow (Arm 2).

Patients will be stratified by treatment target volume. Group 1 will include bone and soft tissue metastasis targets, and Group 2 will include primary or metastatic intrathoracic disease targets.

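### The primary comparison of time in centre ignores the stratification factor, and an undefined normality check, likely to be triggered, decides which test is used

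*Protocol article*

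**What the plan says.** Under Study design, the protocol article states "Patients will be stratified by treatment target volume", with two groups: bone and soft tissue metastases, and intrathoracic disease. The abstract says the same.

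Under Statistical analysis plan, the primary rule is "Comparisons between treatment arms for TIC (primary endpoint) will be performed using the two-sample t-test". The next sentence gives the distributional basis: "TIC data is anticipated to be normally distributed". If the data turn out otherwise, a Wilcoxon rank sum test replaces the t-test where appropriate. No criterion for non-normality is named, and the stratum appears in neither test.

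Under Sample size calculation, "the estimated TIC in the standard arm of this trial will be 4.8 hours, with a standard deviation of 2", and "in the experimental arm, the estimated TIC will be 2.5 hours, with the same standard deviation". The calculation is described as "Using a two-sided, two-sample t-test, with a 1:2 randomization, alpha of 0.05 and power of 80"%, with 10% dropout, giving 33 patients (11 + 22).

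**The concern.** Two features of the stated analysis do not fit the rest of the document.

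First, design and analysis do not match. Stratified allocation balances target volume between the arms. A test that then omits target volume still counts the difference between strata as random error. The estimate of the arm effect is not biased, but its standard error is overstated when target volume predicts TIC. The benefit of stratifying is then partly lost.

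Second, the primary test is left to the data. TIC is an elapsed time, and the planning values for Arm 2 are hard to reconcile with a normal distribution. The fallback is therefore likely to be used in practice, on an undefined judgement made after the outcomes are seen in an open-label trial. The two tests also answer different questions: the t-test concerns the mean difference in hours on which the sample size rests, and the rank sum test does not.

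**Working it through.** **Inputs from the Sample size calculation section.** Means 4.8 and 2.5 h, so the difference is 2.3 h; SD 2 in both arms; allocation 1:2; two-sided alpha 0.05; power 80%; dropout 10%.

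**1. Reproduce the plan's figure.** SE = SD × √(1/n₁ + 1/n₂), noncentrality = 2.3/SE, power from the noncentral t distribution with n₁ + n₂ − 2 degrees of freedom.

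- 9 + 18: SE 0.816, power 77.3%.
- 10 + 20: SE = 2 × √0.15 = 0.775, noncentrality 2.97, power 81.8%.
- 11 + 22: SE 0.739, power 85.5%.

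So 30 evaluable patients are needed, and 30 × 1.1 = 33. The stated sample size reproduces and the planned power is met.

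**2. Effect of omitting the stratum.** The difference in mean TIC between strata, g, is an assumption, because the documents give none. Hold the total SD at 2 and split the strata evenly in each arm. The variance within strata is then 4 − g²/4. The adjusted analysis uses this residual SD with 27 degrees of freedom:

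- g = 0: residual SD 2.00, SE 0.775, power about 82%.
- g = 1 h: residual SD √3.75 = 1.94, SE 0.750, noncentrality 3.07, power 84%.
- g = 2 h: residual SD √3 = 1.73, SE 0.671, noncentrality 3.43, power 91%.

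Simulation of the t-test as written, beside the adjusted model, at 10 + 20:

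| Assumed g | Power, t-test | Power, adjusted | True alpha, t-test |
|---|---|---|---|
| 0 h | 82% | 82% | about 5% |
| 1 h | 82% | 84% | about 4.4% |
| 2 h | 84-85% | 91% | about 2.4% |

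With 30% rather than 50% of patients in the second stratum, the figures at 2 h are 84% vs 90%, with alpha 2.7%. Coverage of the unadjusted 95% interval at 2 h is about 97-98%, so it is too wide. The adjusted analysis stays at about 95% throughout.

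**3. Normality against the planning values.** In Arm 2, Φ((0 − 2.5)/2) = Φ(−1.25) = 10.6%, or 22 × 0.106 = about 2.3 patients with a negative time. In Arm 1, Φ(−4.8/2) = Φ(−2.4) = 0.8%. The Arm 2 values imply right skew.

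**4. How often the switch would operate.** The article names no criterion. Assuming gamma-distributed data at the plan's means and SDs, and Shapiro-Wilk as the check, at least one arm is rejected in about 67% of trials at 10 + 20 and 73% at 11 + 22.

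**5. Whether the skew harms the t-test.** At the planning values and 10 + 20, with pooled variance, power is 81.4% (lognormal) and 80.4% (gamma), interval coverage is 94.5% and 94.8%, and null rejection is 4.3-5.0%. The harm is negligible, so the switch protects against little.

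**The case against.** The strongest reply is that nothing here breaks the trial. The stated 80% power is met. An unadjusted test after stratified allocation is valid and, if anything, conservative. The gain depends on a stratum difference that the documents do not give; up to 1 h it is worth at most about 2 percentage points. Both strata use the same simple planning with at most two fields, so a 2 h difference is not obvious. The Wilcoxon fallback already deals with non-normality in part. A simulation of the switch itself (gamma data, Shapiro-Wilk at 0.05) gave type I error of 5.2-5.3% and power of 87.5%. All of this stands, and it limits the point to efficiency and pre-specification. It does not remove the point, because adjustment costs essentially nothing even when the stratum has no effect. Nor can the matter be left to a separate analysis plan, since the article itself fixes the test and the switching rule.

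A reader might infer more, in three ways.

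- *That the equal-variance assumption contradicts the planning values.* It does not: the plan says "the estimated TIC will be 2.5 hours, with the same standard deviation". Equal SDs imply coefficients of variation of 2/4.8 = 42% and 2/2.5 = 80%, which is open to doubt but not a contradiction.
- *That the intervals would be too narrow.* A pooled 95% interval would cover about 89% if the Arm 2 SD were 1.04 (constant coefficient of variation). That SD appears nowhere in the documents, and the article does not say that the t-test is pooled. At SD 1.04 only 0.8% of a normal curve falls below zero, so this argument cannot be combined with the one on normality. The on-the-day replanning pathway in Arm 2 could also make the larger arm the more variable one, which would reverse the direction.
- *That the trial is underpowered.* Step 1 shows that it is not.

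**Conclusion.** The point holds as a mismatch between design and analysis, together with a data-dependent choice of primary test. The loss is relative to an adjusted analysis and conditional on the stratum effect: none at 0 h, about 2 percentage points at 1 h and about 6 to 7 at 2 h, assuming a total SD of 2, 10 + 20 evaluable patients and strata balanced between the arms. The error is in the conservative direction.

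The tension between the normality assumption and the planned Arm 2 mean and SD follows from the plan's own figures. How often the switch would be used rests on an assumed distribution and an assumed check. The documents support neither a shortfall from the planned power nor a claim that the reported interval would be too narrow.

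**What to change.** Pre-specify one primary analysis: a linear model of TIC on arm and target-volume stratum, fitted by ordinary least squares, reporting the adjusted mean difference in hours with its 95% confidence interval. Delete the switch that depends on a normality check. Report two fixed sensitivity analyses whatever the data look like: a stratified Wilcoxon (van Elteren) test and an unequal-variance version of the comparison.

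The cost is wording and one degree of freedom, with essentially no loss of power if the stratum has no effect (about 82% either way). Robust HC3 standard errors should not be made primary at this sample size. In simulation at 10 + 20 with equal SDs they gave about 77.5% power with no stratum difference, roughly 4 points below the plain t-test, and only about 80% at 1 h. Unequal-variance inference therefore belongs among the sensitivity analyses.

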This proposed feasibility study will evaluate a diagnostic-CT-enabled planning workflow and assess efficacy, acceptability and scalability. The workflow will employ CBCT-planning as a back-up pathway and incorporate optical surface guidance for ease of set-up reproducibility. The study will also expand eligibility criteria from previous work to include thoracic disease targets in addition to bone and soft tissue disease. Pain response or treatment response were not chosen as endpoints given previous evidence of equivalency and/or the reasonable assumption of equivalency as both arms of the investigation ultimately receive the same treatment. The only difference between arms is the planning image set. Thus, the evaluation of the efficacy of the diagnostic-CT-enabled planning workflow, in this context, is dependent upon the rate of plan deliverability (i.e. the experimental planning arm produced a deliverable plan) and acceptability (i.e. the experimental planning arm produced a plan determined to be acceptable as per institutional guidelines).

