#### Plan acceptability

Plan acceptability will be determined by blinded RO review, performed by an expert panel comprised of RO members from the local Palliative Disease Site Team. Because a review of the *planned* dose distribution would not preserve blinding due to visibly apparent characteristics of CT/CT simulation imaging, plan acceptability will be assessed by review of dose distribution of the *delivered* plan shown on the fraction 1 image matching CBCT.

Plan acceptability is defined according to the following local criteria for simple palliative planning:*For parallel-opposed pair plans:*Adequate (as per RO discretion) coverage of the target volume (PTV) by the 90% isodose lineHot spot (maximum point dose) is ≤115% of prescribed dose OR if hot spot is > 115% then the total volume of the hot spot should be <2cm^3^*For single direct field plans:*Adequate (as per RO discretion) coverage of the target volume (PTV) by the 80% isodose lineHot spot (maximum point dose) is ≤125% of prescribed dose OR if hot spot is > 125% then the total volume of the hot spot should be <2cm^3^

Blinded-reviewers will ascribe a score of 1, 2 or 3 to each plan based on the following criteria:AcceptableMinor deviation but still acceptableUnacceptable – plan deficiency may impact clinical outcome

Plan acceptability *does not* refer to clinical judgements such as target delineation, beam arrangement, energy, field borders, shielding, dose/fractionation, etc.

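### The blinded plan review records an ordered 1-2-3 score, but the arms are compared only on an acceptability rate, which on its natural reading cannot register a shift from score 1 to score 2

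*Protocol article*

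**What the plan says.** Under Plan acceptability, the protocol says "Blinded-reviewers will ascribe a score of 1, 2 or 3 to each plan based on the following criteria". The three levels are acceptable, a minor deviation that remains acceptable, and unacceptable. Only the third carries the warning that "plan deficiency may impact clinical outcome".

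The Secondary endpoints section lists this measure as a rate. The Statistical analysis plan section compares the "rate of plan deliverability and rate of plan acceptability on blinded review of dose distributions" between arms: "differences between treatment arms will be compared using the Chi-square test", or Fisher's exact test where appropriate. No comparison that uses the order of the scores is described.

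The Background makes the evaluation of efficacy depend on plan deliverability and plan acceptability. It describes acceptability as meaning that "the experimental planning arm produced a plan determined to be acceptable as per institutional guidelines". Nowhere does the protocol say how the three scores become a rate.

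**The concern.** Score 2 separates a plan that meets the local coverage and hot-spot criteria from one that departs from them slightly. That is a plausible result of planning on a diagnostic scan and then reproducing the patient's position at the treatment unit. If scores 1 and 2 are pooled, this information is collected and never compared between the arms.

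The measure matters because it is the blinded, two-arm view of plan quality. Primary plan deliverability is defined only for the diagnostic-CT plan. With 11 plans in one arm, 22 in the other and probably few scores of 3, a comparison of the rate alone could leave a fairly general loss of quality in Arm 2 untested.

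**Working it through.** **The plan's own figure.** The only sample size statement concerns time in centre: "the estimated TIC in the standard arm of this trial will be 4.8 hours, with a standard deviation of 2", against 2.5 hours "with the same standard deviation". The standardised difference is (4.8 − 2.5)/2 = 1.15. With 10 and 20 evaluable patients the noncentrality is 1.15/√(1/10 + 1/20) = 2.97 on 28 degrees of freedom. Two-sided power at 0.05 is then 81.8%; 9 and 18 patients give 77.3%. Thirty patients × 1.1 = 33, so the stated 11 + 22 is reproduced. (Dividing by 0.9 gives 33.3, rounded up to 34.) No power is stated for plan acceptability.

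**Why the rate misses a 1-to-2 shift.** If acceptable means score 1 or 2, the rate in each arm is p₁ + p₂ = 1 − p₃. Take an assumed 80/15/5% in Arm 1 and 40/55/5% in Arm 2. Both rates are 95%, so a test of the rate can reject only at its type I error.

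**Which test would apply.** With k unacceptable plans in total, the expected number in Arm 1 is k × 11/33. It reaches 5 only when k is at least 15, so Fisher's test is the likely one. With 0/11 unacceptable in Arm 1, it needs 8/22 (36%) in Arm 2 (p = 0.031); 7/22 gives p = 0.067.

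**Power.** Inputs: 11 v 22 plans from the Sample size calculation, taken as all scored; two-sided 0.05; score distributions assumed because the protocol gives none. Under proportional odds, each cumulative probability c in Arm 1 becomes o/(1 + o) in Arm 2, where o = [c/(1 − c)]/OR. For 80/18/2 and OR 5:

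- Score 1: odds 4/5 = 0.8, so 0.8/1.8 = 44%.
- Scores 1 or 2: odds 49/5 = 9.8, so 9.8/10.8 = 91%.
- Arm 2 is therefore 44/46/9% after rounding.

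Power comes from enumerating every possible pair of score counts:

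| Assumed Arm 1 → Arm 2 (scores 1/2/3, %) | Fisher, 3 v 1-2 | Wilcoxon, tie-corrected | Wilcoxon, exact |
|---|---|---|---|
| 80/18/2 → 44/46/9 (OR 5) | 0.06% | 52% | 44% |
| 70/25/5 → 32/47/21 (OR 5) | 4% | 58% | 54% |
| 60/30/10 → 33/42/25 (OR 3) | 6% | 33% | 30% |
| 80/15/5 → 40/55/5 (1 to 2 only) | 0.6% | 55% | 48% |
| 85/10/5 → 65/30/5 (1 to 2 only) | 0.6% | 18% | 13% |
| 80/18/2 → 60/18/22 (1 to 3) | 7% | 22% | 19% |
| 80/15/5 → 40/15/45 (1 to 3) | 62% | 73% | 70% |
| 60/35/5 → 60/10/30 (2 to 3) | 20% | 6% | 5% |
| 50/45/5 → 50/5/45 (2 to 3) | 62% | 15% | 15% |

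An uncorrected chi-square test on score 3 does little better than Fisher in the first three rows: under 1%, 9% and 11%. With equal distributions in both arms, the tie-corrected Wilcoxon test rejects 4.0% of the time (80/18/2) and 4.9% (60/30/10).

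**The case against.** The other side has four good arguments.

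1. **The cut-point is inferred.** A reader might take the protocol to prescribe a yes/no analysis of acceptability. It does not say so; yes or no is specified only for deliverability. The same sentence applies chi-square or Fisher's test to Likert ratings, so a test on the full 2×3 table is conceivable, and it would see a 1-to-2 shift. For 80/15/5 → 40/55/5 the exact 2×3 test has 57.5% power against 47.8% for the exact Wilcoxon. This stands as a reason to state the cut-point. It does not remove the concern, because a 2×3 test is not a comparison of rates. It also ignores order: for 80/15/5 worsened with an odds ratio of 4, it has 23% power against 34%.

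2. **The binary rate answers the protocol's clinical question.** Only score 3 is said to bear on outcome. This stands, and the comparison of the rate should be kept.

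3. **Replacing the rate test with Wilcoxon could hide harm.** When plans move from score 2 to score 3, Wilcoxon is the weaker test (6% v 20%, and 15% v 62%). This stands, and is why the ordered comparison should be supporting only.

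4. **The endpoint is an unpowered secondary one in a feasibility trial.** This also stands. The ordered test is itself weak at this size, with exact power of 13% and 48% for the two pure 1-to-2 shifts tabulated.

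A reader might further infer that a non-significant result will be taken as proof of equal plan quality. The protocol sets no equivalence or non-inferiority rule here and does not say how a null result will be read.

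**Conclusion.** The point holds in a limited form. An ordered score is collected, the stated comparison is of a rate, and on the natural reading that rate cannot register a shift from score 1 to score 2. Under the three assumed proportional-odds worsenings with odds ratios of 3 to 5 in the table's first three rows, power is about 0-6% for Fisher's test on score 3. It is about 33-58% for the tie-corrected Wilcoxon test, or 30-54% in its exact form. These figures illustrate and do not bound the effect: they depend on score distributions that the protocol does not give, and on all 33 plans being scored.

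A general claim that most of the power is lost is not supported. Where many plans move from score 1 to score 3 the difference is modest (62% v 73%), and where they move from score 2 to score 3 the rate comparison is the stronger test. This is an inexpensive improvement to a secondary analysis. It is not an error in the primary design.

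**What to change.** In the Statistical analysis plan section:

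- State that a plan counts as acceptable when its score is 1 or 2.
- Keep the between-arm comparison of that rate as the clinical endpoint.
- Add a prespecified supporting comparison of the ordered 1-2-3 score, by Wilcoxon rank sum test or proportional-odds model.
- Report the number of plans at each score by arm.

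The scores are already collected, and the section already uses the Wilcoxon test for other endpoints, so the change is a sentence or two. The cost is one additional secondary test. A difference driven only by scores 1 and 2 must be described as a difference in quality among acceptable plans; the table of counts will show when that is the case.

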##### Acceptability

Stakeholder evaluation (patients, ROs, medical radiation therapists (MRTs), physicists) using a Likert scale modeled on the Theoretical Framework of Acceptability (version 2) [22]

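### The between-arm chi-square or Fisher test named for stakeholder acceptability does not fit the clinician questionnaires, which come from Arm 2 only and from the same clinician up to three times

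*Protocol article*

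**What the plan says.** The protocol's secondary endpoint for acceptability is defined as "Stakeholder evaluation (patients, ROs, medical radiation therapists (MRTs), physicists) using a Likert scale", so clinicians count alongside patients.

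Under Clinician acceptability, the clinician part "will be assessed within 5 working days of treatment delivery *for Arm 2 patients only". The same section adds: "Clinicians may be asked to complete the questionnaire up to 3 times to inform analysis as to whether perceptions change over time". It also states: "Clinicians will be required to indicate how many times they have previously participated in the dCT-enabled treatment planning workflow on the questionnaire". Completing one questionnaire does not oblige a clinician to complete another.

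Under Patient acceptability, patients are assessed straight after treatment, with no restriction to one arm.

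The Statistical analysis plan then covers all of this in one clause: "acceptability (stakeholder evaluations based on Likert scale), differences between treatment arms will be compared using the Chi-square test or Fisher’s exact test as appropriate". No other method is named for acceptability, and nothing says which of a clinician's responses counts towards the endpoint.

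**The concern.** Two features of the clinician data conflict with the assigned test. First, a comparison of arms needs responses from both arms, and clinicians respond for one arm only. Second, chi-square and Fisher's exact tests assume independent responses, whereas a clinician who answers three times contributes three related ones.

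Acceptability is one of the three things the trial sets out to assess, and change with familiarity is a declared reason for repeating the questionnaire. An analyst who follows the text has no usable method for the clinician data. The easy improvisation is to apply the same tests to Arm 2 questionnaires split by exposure, or to report a simple proportion over all questionnaires. Either would ignore the repeats. The simple proportion would also give most weight to those who chose to answer most often.

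**Working it through.** **The plan's own figure.** The protocol gives no number of clinicians, correlation, effect or power for the questionnaire. Its only computed figure is the sample size for time in centre. The inputs there are "the estimated TIC in the standard arm of this trial will be 4.8 hours, with a standard deviation of 2" and, for the experimental arm, "the estimated TIC will be 2.5 hours, with the same standard deviation". The difference is 4.8 − 2.5 = 2.3 h, or 2.3/2 = 1.15 SD. A two-sided two-sample t-test at 0.05 with 1:2 allocation gives 77.3% power for 9 + 18 and 81.8% for 10 + 20, so 30 evaluable patients are needed. Then 30 × 1.1 = 33, the stated total. That analysis uses one value per patient and is not touched by this point.

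**Step 1: can the named test be run?** It needs a table of arm by response category. Patients can supply both arms. Clinicians supply Arm 2 only, so their Arm 1 row is empty and the test does not exist for them.

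**Step 2: pooled clinician rate, if repeats are treated as independent.** With m responses per clinician and response-scale correlation ρ (assumed), the design effect is 1 + (m − 1)ρ. The true standard error is √(design effect) times the naive one. A nominal 95% interval covers about 2Φ(1.96/√design effect) − 1.

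| m | ρ | Design effect | True/naive SE | Coverage |
|---|---|---|---|---|
| 3 | 0.2 | 1.4 | 1.18 | 90% |
| 3 | 0.3 | 1.6 | 1.26 | 88% |
| 3 | 0.5 | 2.0 | 1.41 | 83% |
| 3 | 0.7 | 2.4 | 1.55 | 79% |
| 2 | 0.2 | 1.2 | 1.10 | 93% |
| 2 | 0.7 | 1.7 | 1.30 | 87% |

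The m = 3 rows are an upper end, because three is the maximum and repeats are voluntary.

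**Step 3: change from first to last response, dichotomised.** Assumptions: 20 clinicians, agreement rising from 60% to 85%, latent correlation ρ, 4,000 simulated data sets per setting.

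| Setting | Chi-square | Fisher | Exact McNemar | Mid-p McNemar |
|---|---|---|---|---|
| ρ = 0.3 | 45% | 31% | 31% | 45% |
| ρ = 0.5 | 41% | 28% | 33% | 46% |
| ρ = 0.8 | 41% | 26% | 37% | 55% |
| ρ = 0.8, 40 clinicians | 77% | 68% | 90% | 95% |

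With no true change and 20 clinicians, chi-square rejects in 5.4% of data sets at ρ = 0, 2.0% at ρ = 0.5 and 0.4% at ρ = 0.8. The unpaired test is therefore conservative. At this size the paired binary tests are conservative too: mid-p McNemar rejects in 3.0% at ρ = 0.5.

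**Step 4: change in a score.** Assumptions: 20 clinicians, shift 0.5 SD.

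- Unpaired t-test: it rejects when the difference exceeds 2.024 × √(2/20) = 0.640 SD. The true SE of the difference is √(2(1 − ρ)/20). At ρ = 0.5 this is 0.224, and (0.640 − 0.5)/0.224 = 0.63, so power is about 27%.
- Paired t-test: 19 df, noncentrality 0.5 × √20/√(2(1 − ρ)). At ρ = 0.5 this is 2.24, so power is 56%.

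| ρ | Unpaired | Paired |
|---|---|---|
| 0.3 | 30% | 43% |
| 0.5 | 27% | 56% |
| 0.7 | 21% | 78% |

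With a shift of 0.7 SD and ρ = 0.5 the gap is smaller in relative terms: 60.5% against 84.4%.

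**The case against.** The strongest reply is that the protocol never assigns these tests to change over time and never promises a pooled clinician rate or interval. It assigns them to differences between arms. The change question is exploratory, and its method may sit in an analysis plan that is not shown. Silence on that method is no fault.

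This stands in part. The losses in steps 2 to 4 follow only if the named test, or a simple proportion, is carried over to clinician data. What the reply does not remove is step 1. The protocol is not silent on clinician acceptability: it includes clinicians among the stakeholders and gives their Likert evaluations a test that their data cannot support.

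Stronger readings are tempting, and the documents do not bear them out:

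- A reader might infer that the change question loses most of its power. That depends on an unstated number of clinicians, correlation and shift. For dichotomised answers at 20 clinicians and ρ = 0.5, chi-square has 41% against 46% for mid-p McNemar, and it beats exact McNemar at 33%. A loss of half or more appears here only for a score, with a correlation of about 0.5 or more and a modest shift. Setting chi-square against an ordinal signed-rank test would also mix lost ordering with lost pairing.
- A reader might cite the Limitations section as admitting that repeat responders are the more enthusiastic. Its remark concerns clinicians who accrue patients, not those who return further questionnaires.
- A reader might infer that repeat questionnaires cannot be linked. One e-consent per clinician, a cap of three and a reported exposure count suggest tracking by person. The article's silence on an identifier is not evidence that none exists.

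**Conclusion.** The point holds as a mismatch between the test and the data. The one method stated for stakeholder acceptability is a between-arm test for independent responses, while the clinician part of that endpoint is one-arm and repeated. As written, the test cannot be applied to clinicians.

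If it were adapted without allowing for repeats, a pooled rate would have a true standard error 18% to 55% above the one reported, assuming three responses each and a response-scale correlation of 0.2 to 0.7. With two responses each the excess would be about 10% to 30%. A test of change would be conservative, with a power loss that is small for dichotomised answers and larger for scores, growing with within-clinician correlation. All these sizes rest on assumed values, since the protocol gives none.

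Neither the primary analysis nor the sample size depends on this, and the interim rule uses plan deliverability rather than questionnaire data. It is a minor correction to a secondary endpoint.

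**What to change.** In the Statistical analysis plan section:

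1. Limit the between-arm chi-square or Fisher's exact test to patient acceptability.
2. Report clinician acceptability as an Arm 2 summary, either from each clinician's first response or from all responses with clinician-clustered intervals.
3. Assess change with exposure within clinician, by a Wilcoxon signed-rank test of last against first response or by an ordinal mixed model with a clinician random intercept and the number of prior exposures as covariate.
4. Confirm that repeat questionnaires are linked by clinician.

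The cost is two or three sentences, with no further participants or questionnaire items, since prior exposure is already recorded. Clinician intervals will be somewhat wider. Clinicians with a single response drop out of the signed-rank test, though they still contribute to the mixed model. A first-response summary describes opinion at the least familiar point, and the report should say so.
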